### Data analysis

SPSS 25.0 will be used for statistical analysis of the data. All collected data will be processed for intention-to-treat analysis. ANOVAs and Chi-Square tests were performed to compare demographic and clinical variables, reasons for attrition, and baseline scores on primary and secondary outcomes between the groups, and significant imbalances between the two groups will be checked. Categorical variables will be explored using chi-square tests, and continuous variables will be analyzed using t-tests or Mann–Whitney U tests, thus exploring baseline differences between the two groups. The number of drop-outs and follow-up losses in both groups will be reported based on descriptive data.

This study will compare the differences in primary and secondary outcomes between the two groups at two time points: baseline and 2 weeks(post-intervention). The generalized estimating equation model (GEE) is a statistical model developed based on the generalized linear model, specifically designed to deal with repeated measures such as longitudinal data. Given the association between outcome variables at multiple time points for individuals in our study, the GEE model will be performed to compare the trends of primary and secondary outcomes at different time points (baseline, 1 week, 2 weeks, 1 month, and 6 months) in the two groups, adjusted for confounding factors of statistical differences in the baseline. The GEE model will be applied to explore the effects of time factors, intervention factors, and interactions between intervention factors and time factors on each variable between the two groups. When there is an interaction effect, then the analysis of the simple effects will be adopted. In this study, no subgroup analysis will be performed. To reduce the risk of type I errors, Bonferroni correction will be used for multiple comparisons, that is, dividing 0.05 by the number of comparisons. Thus, *P* < 0.01 represents a statistically significant difference.

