**Methods:**

This is an assessor-blinded randomized controlled trial following the SPIRIT guidance. A total of 84 depressed patients will be recruited from the inpatient wards of a psychiatric hospital and randomly assigned to the control and experimental groups. Patients in the control group will be treated as usual. In contrast, patients in the experimental group will receive 6 sessions of the PPSF intervention for two weeks on top of the routine care. Primary outcomes are psychological pain, hope, cognitive distortions. Secondary outcomes are depression and suicidal ideation. Data will be collected at 5-time points: baseline, 1 and 2 weeks (post-intervention), 1 month (follow up), and 6 months after baseline. Generalized equation evaluation will be used to assess the effectiveness of the PPSF intervention.

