### Sample size and recruitment

In this study, the primary outcome of the psychological pain score was selected to calculate the effect sizes. Based on the literature [20], the post-intervention psychological pain score measured using DT was 1.5 ± 0.98 for the experimental group and 2.3 ± 1.05 for the control group, with a statistically significant difference, and an effect size d of 0.788 was calculated. In the G*Power software, the number of participants in each group sample was calculated as 35 cases by using two independent samples t-test and taking bilateral α = 0.05 and 1-β = 0.9. Considering a dropout rate of 20%, the minimum sample size was therefore derived as 84 patients, 42 in each group.

Nurses will introduce the study to depressed inpatients who meet the inclusion criteria, and if a patient agrees verbally to participate, nurses will notify the researchers. The researchers will explain the information about the study in more detail to participants, discuss the appropriate timing of the intervention, and provide informed consent. Then, the participant will return the signed informed consent to the researchers. Participants will be recruited from June 2022 to June 2023, and once recruited, patients will be randomly assigned to the experimental or control group.

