#### Other information

Other information included demographic information, clinical variables of patients, and reasons for dropout. Among them, demographic information includes participants’ gender, age, religion, education level, marital status, occupation, interpersonal relationship, and family history; Clinical variables include the type of diagnosis and medication prescribed for patients with depression. These two pieces of information are collected at the baseline. The reasons for attrition will be tracked and collected by researchers during the intervention.

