### Data collection

The data collection for this study will be independently accomplished by a trained nurse who will be blind to recruitment and allocation. The study will measure outcomes at 5 time points: baseline, 1 and 2 weeks (post-intervention), and 1 month and 6 months after baseline (follow-up). The schedule of the study is shown in Table 2. As depressed inpatients are commonly hospitalized for 2–3 weeks, the first 3 measurements will be handed out on the spot in the ward, filled in, and collected. The last 2 measurements will be collected by appointment with patients in the outpatient clinic. All questionnaires will be issued in paper form and will be archived by special researchers after collection. If patients leave the wards earlier than 3 weeks, they will not be allowed to complete the questionnaire 3 times in the ward, and data collection will be completed by appointing patients to the outpatient clinic. Participants in the control group will also be required to complete the measurements at the same time points.

**Table 2 Tab2:** Schedule of enrolment, intervention, and outcome assessment

**Timepoint**	**Enrolment**	**Allocation**	**Post-allocation**				**Filler**
	-T_1_	T_0_ baseline	T_1_ 1st week	T_2_ 2nd week	T_3_ 1st month	T_4_ 6th month	

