## Limitations

To our knowledge, this study comes with some limitations. Firstly, because the study will use a psychological intervention that will be difficult to blind patients and researchers, an assessor-blinded randomized controlled trial will be used, which may result in potential bias. Secondly, this study will involve six psychological interventions over a 2-week period, which may be too intensive, and have a 6-month follow-up, which may result in patients dropping out. Thirdly, the participants in this study were from only one psychiatric hospital, which can affect generalizability. Finally, since this study will be conducted in one hospital, this will inevitably lead to contamination between groups, affecting the results. However, if differences in findings between the two groups are finally shown, it will indicate that the PPSF intervention is still effective even in contamination.

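### GEE as the main longitudinal analysis at about 34 patients per arm: with the usual robust variance the group-by-time test runs at about twice its 1% level, and 6-month estimates can be biased if an independence working correlation meets dropout that differs by arm

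*Protocol article*

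**What the plan says.** The abstract makes GEE the effectiveness analysis: "Generalized equation evaluation will be used to assess the effectiveness of the PPSF intervention". Data analysis repeats this for all five visits ("the GEE model will be performed to compare the trends of primary and secondary outcomes at different time points"). It tests time, intervention and "interactions between intervention factors and time factors on each variable between the two groups", and moves to simple effects when the interaction is present. The significance threshold is P < 0.01, and the analysis is called intention-to-treat. The same section also plans a separate group comparison at baseline and 2 weeks.

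On dropout, Sample size and recruitment says: "Considering a dropout rate of 20%, the minimum sample size was therefore derived as 84 patients, 42 in each group". Limitations remarks that six sessions in two weeks may be too demanding and that the trial will "have a 6-month follow-up, which may result in patients dropping out". Data collection places the first three assessments in the ward and the last two at outpatient appointments.

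On reasons for loss, Other information says: "The reasons for attrition will be tracked and collected by researchers during the intervention". Data analysis then compares those reasons between the arms.

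**The concern.** Two properties of GEE matter here.

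- **Small samples.** The usual robust (sandwich) variance is too small on average when there are few patients, and a chi-square reference ignores that it was estimated. The effect grows with the number of contrasts tested jointly. The joint interaction test is the one that decides whether simple effects are examined, for each outcome.
- **Dropout.** GEE on available data is guaranteed in general only when dropout is unrelated to earlier scores, or is explained by covariates in the model. Return to an outpatient clinic at 1 and 6 months may depend on how the patient is doing. Only the PPSF arm receives the six sessions, so a difference in dropout between arms is plausible.

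At stake are the error rate of the gatekeeping test and the size of the follow-up differences, chiefly at 6 months.

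A smaller matter sits beside these. If reasons are collected only while the intervention runs (weeks 1 and 2 in Table 2), the planned comparison of reasons cannot cover losses at 1 and 6 months.

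**Working it through.** **1. The plan's own sample size.** The inputs from Sample size and recruitment are 1.5 (SD 0.98) versus 2.3 (SD 1.05), two-sided α = 0.05 and power 0.90.
- Pooled SD = √[(0.98² + 1.05²)/2] = 1.0156, so d = 0.8/1.0156 = 0.788, as stated.
- A two-sample t-test (noncentral t) needs 35 per arm (power 0.901), as stated.
- 35 × 1.2 = 42 per arm, 84 in total, as stated.
- Expected to remain at 20% loss: 42 × 0.8 = 33.6, about 34 per arm.

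**2. Size of the interaction test.** Two arms and five visits, with time categorical, give (2 − 1) × (5 − 1) = 4 degrees of freedom. For complete normal data, equal arms and independence GEE, the size can be written down. With N = 68 and ν = 66, the Wald statistic times 66/68 is a Hotelling T², and T² × (ν − 3)/(4ν) follows F(4, 63). The chi-square cut-off c therefore corresponds to F = c × (66/68) × 63/(4 × 66) = c × 63/272.

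| Nominal | c | F | True size |
|---|---|---|---|
| 5% | 9.488 | 2.198 | 7.9% |
| 1% | 13.277 | 3.075 | 2.2% |

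For a single contrast, the z cut-off times √(66/68) is referred to t with 66 degrees of freedom. 1.960 becomes 1.931 (true size 5.8%), and 2.576 becomes 2.538 (true size 1.4%).

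Simulation covered 34 complete patients per arm, or 42 per arm with 20% loss. Working correlations were independence, exchangeable and unstructured; assumed true correlations were exchangeable 0.5 and AR(1) 0.7. It gives the same picture:
- 4-df interaction: 7.1–9.1% at nominal 5% and 1.9–2.5% at nominal 1%.
- Single contrasts: 4.7–6.6% and 1.0–1.7%.

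Multiplying the sandwich variance by n/(n − 2) and using a t or F reference brings the interaction test to 4.2–5.4% and 0.8–1.2%.

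**3. Bias at 6 months.** The documents give no correlations and no dropout mechanism, so these are assumptions: about 20% loss by 6 months, depending on the last observed score.

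| Dropout pattern | Independence | Exchangeable or unstructured |
|---|---|---|
| Same in both arms | about 0 | about 0 |
| Score-related in one arm only | about 0.12 SD | at most about 0.02 SD |
| Opposite directions | 0.18–0.20 SD | at most 0.04 SD |
| Opposite, stronger dependence | 0.27–0.32 SD | at most 0.04 SD |

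These figures are for no true effect. In the opposite-direction settings under independence, the 6-month contrast rejects 10–24% of the time at nominal 5%.

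With a true 6-month effect of 0.40 SD, independence GEE returned 0.08–0.21 for opposite directions (bias 0.19–0.32) and 0.23–0.31 for one arm only (bias 0.09–0.17). A likelihood mixed model returned about 0.40 in a comparable opposite-direction setting.

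**4. Reasons for attrition.** Other information limits collection to the intervention period. Data analysis compares reasons between arms and also reports follow-up losses. As worded, the two do not cover the same period.

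**The case against.** The strongest reply is that the bias belongs to one option, the independence working correlation, which the article does not name. Data analysis justifies GEE by the association between repeated scores, which if anything points away from independence. An article commonly leaves the working correlation, any weighting and the variance correction to a fuller document. This stands: silence on these is not an error, and the bias can only be stated conditionally.

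Material bias also needs dropout that differs by arm, and no passage says that dropout will depend on scores. That stands too. Where worse controls and better PPSF patients leave, the benefit is understated rather than invented. But the documents do not fix the direction, and the reverse pattern would overstate it.

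The powered comparison is the post-intervention one, and the first three assessments are planned in the ward, so the 2-week result is less exposed. And a 2% interaction test is still below 5%. Both are true, but 1% is the level the plan sets for itself, and the liberal test is the one that opens the simple effects.

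Finally, GEE can be repaired without being replaced. That is correct, and the fix offers it as an alternative.

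**Conclusion.** The point holds in limited form. With the usual uncorrected variance, the stated method has a group-by-time test at about 2% instead of 1% (about 8% instead of 5%) with 34 per arm. This follows from the design and needs no dropout assumption. Single contrasts are only slightly off. Bias of roughly 0.1 to 0.3 SD at 6 months is conditional on an independence working correlation together with score-related dropout that differs by arm; otherwise it is negligible.

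A reader might infer more than the documents support:
- *That GEE is valid only under completely random dropout.* That is where its general guarantee ends. With these continuous scores and a non-independence correlation, bias was at most 0.04 SD in the settings examined.
- *That 20% dropout over 6 months is planned.* The sample size section gives no time horizon. Six months is an inference from Limitations.
- *That the protocol expects the PPSF sessions to drive patients out.* Limitations raises intensity and follow-up length only as possibilities.
- *That every robust test is badly liberal.* Only the joint interaction test is materially so.

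The change is worth making before analysis, because a better-behaved method is available in the same software at little cost.

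**What to change.** **Preferred.** Make the main longitudinal analysis a likelihood-based mixed model for repeated measures: SPSS MIXED, REML, unstructured covariance, Satterthwaite degrees of freedom, with group, visit and group × visit. Include every randomised patient with any score, keeping baseline as a response with a mean common to both arms. Restricting the set to patients with a post-baseline score would exclude randomised patients from an analysis called intention-to-treat. Keep GEE with a non-independence working correlation as a sensitivity analysis.

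**Alternative.** Keep GEE as the main analysis, but state an unstructured working correlation and a small-sample variance correction with t or F reference.

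**Separately.** In Other information, extend collection of reasons for attrition through 6 months, so that the between-arm comparison covers follow-up losses. Make this change early, because reasons not recorded at the time may not be recoverable.

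**Cost.** A few sentences and slightly more programming in the same software. The mixed model relies on roughly normal residuals for these summed scores and on data missing at random; it does not protect against dropout that depends on unobserved scores.

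### GEE covariates are chosen by baseline significance tests, with no commitment to adjust for each outcome's own baseline score, which costs precision

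*Protocol article*

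**What the plan says.** All of this stands in the Data analysis section of the protocol article unless noted.

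- **Baseline tests.** Significance tests are applied to patient characteristics and to "baseline scores on primary and secondary outcomes between the groups, and significant imbalances between the two groups will be checked".
- **Model.** A GEE compares the outcomes "at different time points (baseline, 1 week, 2 weeks, 1 month, and 6 months) in the two groups" and examines "the effects of time factors, intervention factors, and interactions between intervention factors and time factors on each variable". Baseline is therefore one of the five response times.
- **Covariates.** The model is "adjusted for confounding factors of statistical differences in the baseline". No sentence commits to adjusting an outcome for its own baseline score.
- **Contrasts.** "When there is an interaction effect, then the analysis of the simple effects will be adopted". Separately, the two groups are to be compared at baseline and again at 2 weeks.

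The section on randomization and masking adds that covariate effects will be controlled by balancing baseline characteristics. Allocation is by simple randomisation, and no balancing method is named. The rule in Data analysis is thus the only stated mechanism.

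**The concern.** In a randomised comparison, a baseline P value below 0.05 reflects the luck of the allocation. It measures imbalance, not how strongly a variable predicts the outcome. The rule can bring in an irrelevant variable that happened to differ and leave out a strongly prognostic baseline score at P = 0.06. The adjustment set is unknown until the data are seen.

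The outcome's own baseline score is usually the most useful covariate, and here it enters only if it happens to differ significantly. At stake is precision in an 84-patient trial with a stated significance threshold of 0.01, and the error in the estimate when the arms differ at baseline by an amount that the tests do not flag.

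The article states this rule outright, so it is not a detail left to an unseen analysis plan. A plan that follows the rule inherits the problem, and one that does not contradicts the article.

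**Working it through.** **Inputs.** From Sample size and recruitment: post-intervention scores 1.5 (SD 0.98) and 2.3 (SD 1.05), d = 0.788, two-sided 0.05, power 0.90, 42 per arm, 20% dropout. From Data analysis: threshold 0.01. Assumptions: baseline-to-2-week correlation ρ of 0.3, 0.5 or 0.7 (not given in the article); equal SDs at the two times; the full 20% dropout by 2 weeks, which leaves 42 × 0.8 = 33.6 per arm.

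**The plan's own figure.** Pooled SD = √((0.98² + 1.05²)/2), so d = 0.8/1.016 = 0.788. The noncentral-t power of a two-sample t-test with 35 per arm is 0.901, so 35 per arm reproduces.

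**What the planned contrasts estimate.** A GEE with group, time and group × time was fitted to simulated complete data. The group × time term at a visit equalled the between-arm difference in change from baseline. The simple effect at a visit equalled the raw difference at that visit. Neither is baseline-adjusted unless the significance rule happens to add the baseline score.

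**Variance per arm, in units of SD².** Raw 2-week score: 1. Change: 2(1 − ρ). Baseline-adjusted: 1 − ρ². The reduction is ρ² against raw and 1 − (1 + ρ)/2 against change.

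**Power at two-sided 0.01.** Noncentral t with 2 × 33.6 − 2 = 65.2 degrees of freedom and noncentrality (0.788/√variance) × √(33.6/2). For the raw contrast this is 0.788 × 4.099 = 3.23.

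| ρ | Raw variance | Change variance | Adjusted variance | Cut vs raw | Cut vs change | Power raw | Power change | Power adjusted |
|---|---|---|---|---|---|---|---|---|
| 0.3 | 1 | 1.40 | 0.91 | 9% | 35% | 72% | 53% | 77% |
| 0.5 | 1 | 1.00 | 0.75 | 25% | 25% | 72% | 72% | 86% |
| 0.7 | 1 | 0.60 | 0.51 | 49% | 15% | 72% | 93% | 97% |

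The direction does not depend on the assumed ρ. Raw minus adjusted is ρ², and change minus adjusted is (1 − ρ)². Both are positive for any ρ strictly between 0 and 1.

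**Effect of an unflagged baseline gap.** With 42 per arm, the largest gap that stays non-significant at 0.05 is 1.989 × √(2/42) = 0.43 SD. The expected absolute gap is √(2/42) × √(2/π) = 0.17 SD. A gap shifts the raw contrast by ρ × gap and the change contrast by (ρ − 1) × gap.

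- At ρ = 0.5, a gap of 0.43 SD shifts the raw contrast by +0.22 SD and the change contrast by −0.22 SD. The expected gap shifts them by about +0.09 and −0.09 SD.
- At ρ = 0.7, a gap of 0.43 SD shifts them by +0.30 and −0.13 SD.

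**Simulation** (40,000 trials per ρ, 42 per arm, no true effect). Among trials with a non-significant gap above 0.2 SD (mean 0.29 SD), the average raw, change and adjusted estimates were +0.14, −0.15 and 0.00 at ρ = 0.5, and +0.20, −0.09 and 0.00 at ρ = 0.7. A rule that adjusts the 2-week difference only when the baseline test is significant had variance 0.0442 against 0.0360 for always adjusting at ρ = 0.5 (23% larger). At ρ = 0.7 it was 0.0406 against 0.0242 (68% larger).

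**The case against.** Several stronger readings are tempting, and the article does not support them.

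- **That chance imbalance goes uncorrected throughout.** This is true of the raw 2-week comparison, the simple effects and any prognostic covariate that is not selected. It is not true of group × time, which subtracts the outcome's own baseline gap in full and so errs in the other direction.
- **That the treatment estimate is biased.** Over randomisations the raw and change contrasts are unbiased. The error is conditional on the gap observed, and nothing here shows an inflated type I error.
- **That the effect is diluted by 20%.** A constant post-baseline effect averaged over five times, one of which is baseline, would shrink to 4/5. But the article does not name the group main effect as the treatment effect. It names a 2-week comparison, and simple effects when there is an interaction.
- **That baseline must not be a response.** A model with baseline as a response is valid if the arm means are constrained equal there. The article states no such constraint, but the choice of response times is not in itself an error.
- **That a baseline score would appear on both sides of the model.** The article does not say whether an outcome's own baseline counts as a confounder in its model. A significant difference would arise by chance in about 5% of trials per outcome.

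Two points on size also stand. The 0.43 SD gap is a boundary case. And against the change contrast at ρ = 0.7, adjustment raises power only from 93% to 97%. Entry cut-offs on OMMP and HAMD-24 probably lower ρ for those two outcomes, and at ρ = 0.3 the gain over the raw contrast is 72% to 77%.

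None of this defends choosing covariates by significance.

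**Conclusion.** The point holds as one of efficiency and prespecification. The selection rule is data-driven, is unrelated to prognostic strength and omits the one covariate measured for every outcome. For any correlation strictly between 0 and 1, prespecified baseline adjustment is more precise than either planned contrast. At an assumed correlation of 0.5 it takes power at the 0.01 threshold from 72% to 86%, whichever planned contrast is used. At 0.3 the larger gain is over change, and at 0.7 it is over the raw contrast.

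These sizes rest on the assumed correlation, on the planned effect of 0.788 carrying over to the outcome analysed, and on 33.6 patients per arm at 2 weeks. The change is worth making because it is free. It does not mean that the planned comparison is invalid.

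**What to change.** Replace the significance-based covariate rule with prespecified adjustment for each outcome's own baseline score, whatever the observed imbalance. Either form will do:

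1. Model the outcome at 1 week, 2 weeks, 1 month and 6 months, with group, visit, group × visit, that outcome's baseline score and baseline × visit.
2. Keep baseline as a response and constrain the arm means to be equal at baseline.

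Name any other prognostic covariates in advance. Do not use baseline tests to choose covariates; a descriptive baseline table is enough. State that the treatment effect is the baseline-adjusted 2-week contrast.

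The cost is analysis wording only. Table 2 of the article already schedules all five outcomes at T0, so no new data are needed.

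### The five-visit GEE examines a group effect that takes in baseline beside the group-by-time interaction, and names neither term as the one that shows efficacy

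*Protocol article*

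**What the plan says.** The Methods part of the abstract names the GEE as the efficacy analysis: "Generalized equation evaluation will be used to assess the effectiveness of the PPSF intervention".

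The Data analysis section then sets the following:

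- The GEE compares trends "at different time points (baseline, 1 week, 2 weeks, 1 month, and 6 months) in the two groups", so baseline is a response visit.
- For each outcome it will "explore the effects of time factors, intervention factors, and interactions between intervention factors and time factors on each variable between the two groups".
- The only follow-up rule is "When there is an interaction effect, then the analysis of the simple effects will be adopted". Nothing is said for the case without an interaction.
- The model is "adjusted for confounding factors of statistical differences in the baseline". The baseline outcome scores are among the variables tested for imbalance.
- For multiplicity, "Bonferroni correction will be used for multiple comparisons, that is, dividing 0.05 by the number of comparisons", which leads to a limit of P < 0.01.

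The same section also announces a comparison of the two groups at baseline and at 2 weeks, apart from the GEE.

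**The concern.** A treatment can change only what is measured after it starts. In a group-by-time model with baseline among the responses, the treatment effect lies in how the group difference changes from baseline, or in the later difference adjusted for the baseline score. The group main effect is neither. If there is no interaction, the group difference is the same at baseline as afterwards, so a significant group row describes a difference that existed before the first session. If PPSF works, the baseline visit, where the effect is zero, pulls the group row towards zero.

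The article lists this term beside the interaction, under one significance limit, in the analysis that is to assess effectiveness, and ranks neither. A reader of the results could take either row as the answer. That leaves two routes to a positive finding per outcome, one of which measures the treatment effect poorly.

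**Working it through.** **Inputs.** From Sample size and recruitment: d = 0.788, 35 per group before dropout, 42 after. From Data analysis: five visits including baseline, limit 0.01. Assumed, because the documents give no figure: factorial coding, complete data on 35 per arm, unit variance, the same effect at all four later visits, and visit correlation r of 0.3, 0.5 or 0.7 (exchangeable), with a first-order autoregressive pattern of 0.7 as a variant.

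**The plan's own figures.** Pooled SD = √((0.98² + 1.05²)/2) = 1.016, so d = 0.8/1.016 = 0.788. A two-sided t-test at 0.05 with 35 per group has power 0.901. 35 × 1.2 = 42 per group, 84 in all. 0.05/5 = 0.01. All are reproduced.

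**Dilution.** Baseline has weight 1/5 and effect zero, so the averaged group effect is (0 + 4 × 0.788)/5 = 0.63 SD.

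**Power at two-sided 0.01** (critical value 2.576, known variance). The squared standard error is (2/35) × v, with:

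- group effect averaged over five visits: v = (1 + 4r)/5, effect 0.63
- baseline-adjusted mean of the four later visits: v = (1 + 3r)/4 − r², effect 0.788
- 2-week difference adjusted for baseline: v = 1 − r², effect 0.788
- 2 weeks versus baseline, group-by-visit contrast: v = 2(1 − r), effect 0.788

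| r | Averaged group effect | Adjusted mean of later visits | Adjusted 2-week difference | 2 weeks versus baseline |
|---|---|---|---|---|
| 0.3 | 92% | 99.7% | 81% | 58% |
| 0.5 | 80% | 99.8% | 89% | 76% |
| 0.7 | 67% | 100% | 98% | 95% |
| 0.7, autoregressive | 78% | 98.5% | 89% | 75% |

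For example, at r = 0.5 the averaged group effect has standard error √(0.0571 × 0.6) = 0.185; 0.630/0.185 = 3.40; 3.40 − 2.576 = 0.83, which gives 80%. Simulation of the first two columns gave 68-91% and 98.5-100%, in agreement to about one point. The last two columns are single-visit contrasts and were worked out by formula only.

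**Two routes.** With no PPSF effect and each term tested at 0.01, independence gives 1 − 0.99² = 1.99% per outcome. Simulation gave 2.0-2.1% for either term, against 1.0-1.1% for each alone. With an uncorrected sandwich variance the rate for either term was 3.3-3.7%. Part of that is small-sample behaviour of the sandwich, since the interaction alone was then at 2.1-2.4%.

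**Chance baseline difference, no effect.** Over all randomisations the group test stays at 1.0-1.1%. Given a particular baseline difference, it reaches P < 0.01 in:

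- 0.1-1.0% of trials at 0.3 SD
- 1.0-2.3% at 0.4 SD
- 5.8-6.6% at 0.5 SD

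The baseline-adjusted mean of the later visits stays near 1% throughout. With 42 per arm, a baseline difference above 1.96 × √(2/42) = 0.43 SD is significant at 0.05.

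**The case against.** The strongest objection is that the article lists three standard model terms and attaches no decision rule to the group row. The verb is exploratory, the stated purpose is to compare trends (the interaction question), and the only follow-up rule hangs on the interaction. This stands in part. A reader might infer that a significant group effect will be declared as PPSF efficacy, but no sentence says so. What the text does is leave that open in the analysis it assigns to effectiveness.

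Second, a reader might infer that without an interaction the whole result rests on the group row. That is not supported either, because the separate baseline and 2-week comparison does not depend on the interaction.

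Third, a reader might infer that baseline imbalance inflates the type I error. It does not: the group test keeps 1% over all randomisations, and the higher rates arise only given an imbalance. The planned adjustment for significant baseline differences may catch those above about 0.43 SD, if 0.05 is the limit used for the baseline checks, which is not stated. Smaller ones pass, and adjusting for the baseline score would still leave baseline in the averaged response.

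Fourth, a family-wise error near 10% (ten tests at 0.01, sum 0.10) would require that both terms count as successes and that the divisor of five means the five outcomes. The article states neither, so that figure is not claimed here.

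Finally, the averaging depends on coding. With baseline as the reference visit the group term is the baseline difference alone; with another reference visit it is the difference at that one visit, not corrected for the baseline score. Neither coding turns the term into a sound measure of efficacy.

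Naming the decisive contrast could be left to an analysis plan. But the article itself includes a term that measures the treatment effect poorly and puts it on the same footing as the interaction, which goes beyond missing detail.

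**Conclusion.** The point holds in limited form. The GEE as described examines a group effect that, under the usual coding, takes in the pre-treatment visit, and it does not say whether this term or the interaction shows efficacy. A group effect without an interaction is not evidence for PPSF. A sustained effect of 0.788 SD is shown 20% too small, and power at 0.01 is about 68-91% where a baseline-adjusted mean of the same later visits has 98.5-100%. If either term may support a claim, the false-positive rate per outcome is about 2% instead of 1%.

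These sizes rest on factorial coding, complete data, 35 per arm, a constant effect from week 1 to month 6, and visit correlation 0.3-0.7. If the effect is smaller at 1 week or has faded by 6 months, the averages over visits shrink further. The defect should be corrected, but the documents do not show that a false claim of efficacy is planned.

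**What to change.** State in Data analysis that the group and time main effects of the five-visit GEE are descriptive and will not be used to claim a PPSF effect. Let one contrast per outcome decide: the 2-week group difference adjusted for the baseline score, whether or not that score differs significantly between groups. The group-by-visit contrast of 2 weeks versus baseline is an alternative, but has less power at every correlation shown. Either fits the 2-week comparison already planned and the post-intervention score on which the sample size rests. The 1-week, 1-month and 6-month contrasts are then supportive.

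The near-100% power above belongs to the average over four later visits, not to a single visit. The adjusted 2-week difference has about 81-98% under the same assumptions, which at r = 0.3 is below the averaged group effect. The reason to choose it is that it measures the treatment effect at the planned time. If an overall effect is wanted instead, average the group difference over the post-baseline visits only, adjusted for the baseline score, and fix that choice in advance.

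The cost is one or two sentences before unblinding, with no new data or patients. The small downside is that the sponsor gives up one route to a significant result.
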